#### Interim analyses {21b}

We will conduct interim analyses between follow-up assessments to monitor changes in IPV and depression severity to ensure that there is no unintended increase in either outcome. Additionally, we will document any adverse or serious adverse events to ensure participant safety and assess any potential risks associated with the MILAP.

#### Methods for additional analyses (e.g. subgroup analyses) {20b}

We do not plan to conduct any additional analyses other than those mentioned above.

#### Methods in analysis to handle protocol non-adherence and any statistical methods to handle missing data {20c}

The scenarios that are not covered by the trial protocol or those that require deviation from the protocol will be discussed within the team and will proceed with the approval of the principal investigators (PIs). We will document all such scenarios and decisions.

We will employ multiple imputation methods if missingness can be assumed to be (completely) at random for the primary analyses.(88) Alternatively, and depending on the type of analysis at hand (e.g. structural equation model), we will use full information maximum likelihood estimation.(89)

#### Plans to give access to the full protocol, participant level-data and statistical code {31c}

In compliance with the current National Institutes of Health Data Management and Sharing Policy, we will submit de-identified quantitative participant-level data to the National Institute of Mental Health (NIMH) Data Archive no later than one year after study completion. Additionally, we will share data and statistical code for quantitative analyses and codebook information for any qualitative data used in any publications at the time of publication.

### Oversight and monitoring

#### Composition of the coordinating centre and trial steering committee {5d}

Per the contractual obligations with the funder and institutional regulations, the tasks of coordinating centre and trial steering committee are conducted by a board described in the next section.

#### Composition of the data monitoring committee, its role and reporting structure {21a}

We will establish a five-member independent data safety and monitoring board led by an expert in mental health and IPV interventions. The board members will meet biannually to review safety procedures, ensure confidentiality protocols, and uphold participant protection standards.

### Safety monitoring & management

We will implement a standardized risk management system informed by findings from MILAP pilot studies, guidance from the community advisory board, and prior mental health research conducted by our team. During each intervention and assessment session, counselors and assessment staff will check in with participants regarding any recent incidents of IPV or other safety concerns. Any cases requiring urgent attention will be managed according to a pre-established crisis counseling and referral protocol.

During each assessment, assessment staff will administer PHQ-9, which includes a question on suicidality, to women participants. If a participant indicates any risk of suicidality, the assessment staff will administer the NESS-3. Patients identified as being at high and acute suicide risk will be immediately connected with a contracted crisis counselor for further evaluation and support. If immediate intervention is required, we will coordinate with the participant’s emergency contact and refer them to tertiary care facilities or OCMCs in their district. If no urgent referral is needed, the participant will be provided with a resource card containing contact information for relevant support services. In both scenarios, a study team member and the crisis counselor will follow up within 48 hours to ensure the participant’s safety and well-being. Severe IPV cases requiring medical attention will be referred to OCMCs at tertiary hospitals for mental health services, legal aid, medical care, shelters, and support from the community-based organizations. We will connect women in need of shelter support to WOREC for safe house services.

The study team will document all these incidents on standardized forms. The Principal Investigators (PIs) will review these reports and adjust safety protocols as needed. The data and safety monitoring board will conduct semi-annual evaluations to ensure the safety of participants throughout the study.

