**Methods:**

This RCT will enroll 300 family triads, each comprising of a young married woman (aged 15–24), her husband, and her MIL. Blinded staff will conduct baseline assessments, after which each triad will be randomly assigned to either the MILAP or Enhanced Usual Care (EUC). MILAP comprises nine sessions delivered by trained psychosocial counselors and focuses on strengthening the supportive relationship between MILs and daughters-in-law (DILs), providing behavioral couples therapy, and enhancing overall family dynamics. EUC includes standard care, such as individual and group counseling for IPV, enhanced with crisis counseling and referral support to ensure participant safety and access to additional resources. All participants, regardless of intervention allocation, will be assessed at baseline and at 1, 3, 6, 9, and 12-month follow-ups. These assessments will measure: primary outcomes [depression using Patient Health Questionnaire-9; IPV using Indian Family Violence and Control Scale], secondary outcome [post-traumatic stress disorder (PTSD) using PTSD CheckList-Civilian Version], and other outcomes. We will also conduct serial in-depth interviews to explore the mechanisms underlying MILAP’s effectiveness and perform a cost-effectiveness analysis to assess its potential for scalable implementation.

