### Interventions

#### Explanation for the choice of comparators {6b}

**MILAP** is an innovative family-based intervention involving married woman, her husband, and MIL. Spanning nine weeks (11 total hours), MILAP addresses women’s current experiences of IPV and mental health needs by incorporating communication skills, stress management techniques, and strategies to strengthen relationships. We will compare MILAP with currently available IPV services, i.e., EUC delivered by WOREC. EUC builds on standard individual and group counseling by adding crisis counseling and streamlined referral mechanisms to ensure participants’ safety and facilitate access to comprehensive medical and psychosocial support.

As this is a 1:1 randomized trial, half of the total study participants (150 family triads; 450 individuals) will receive MILAP, while the remaining half will receive EUC.

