#### Intervention description {11a}

##### Multi component family Intervention to Lower depression and Address Intimate Partner violence (MILAP):

The MILAP, summarized in Table 1 below, includes nine sessions delivered over nine weeks to young women aged 15–24, their husbands, and MILs.

All sessions will be delivered by counselors who have completed at least six months of psychosocial training and received specialized training to deliver MILAP from master’s-level psychologists and senior researchers. The sessions will take place in community-based counseling centers operated by either WOREC or local government, depending on participant convenience. MILAP is divided into three sections: MIL-DIL sessions, BCT sessions, and a triad summary session.

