##### Enhanced usual care (EUC):

EUC will be delivered by a separate team of counselors who have completed at least six months of psychosocial training but have not received specialized MILAP training, in order to avoid potential contamination. These counselors will conduct an initial safety assessment and offer: a) WOREC’s IPV rehabilitation services, which include access to a women’s shelter, safety and protection from the perpetrator, mental health counseling, legal support, and health services; b) educational materials on safety planning, the consequences of ongoing IPV, written resources for reducing IPV, and information about a nationwide IPV/DV hotline; c) referrals to wraparound services based on the woman’s needs and priorities, including legal support, safe housing, psychosocial counseling, health services, and livelihood support; d) referral to a one-stop IPV center, along with information about available options, including support for leaving the relationship if the participant expresses that desire.

Since this study includes women currently experiencing IPV, we will enhance the usual care by adding two key services: mental health crisis counseling and a referral pathway for those in need of specialized support.

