#### Participant timeline {13}

After the consent process is completed, we will conduct baseline assessments. This will be followed by the 1:1 random allocation of the recruited participants to either MILAP or EUC. Participants will then receive the intervention based on their allocation. We will conduct follow-up assessments at 1, 3 6, 9, and 12 months from baseline for all participants, regardless of intervention allocation. To evaluate the effectiveness of individual MILAP components, the one-month follow-up assessment will take place immediately after the completion of all MIL-DIL sessions and prior to the start of the BCT sessions. The three-month follow-up will be conducted after participants have completed all nine MILAP sessions. Figure 2 below shows the study timeline.

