#### Confidentiality {27}

To ensure confidentiality in data collection and management, we will use the HIPAA-compliant REDCap mobile application on password-protected tablets for secure collection of responses. We have trained research assistants, assessment staff and counselors on maintaining participant confidentiality. We will assign different level of responsibility and REDCap login to safeguard data security, privacy and confidentiality. Login access will be managed through a two-factor authentication system and each user will be granted role-specific access (entry, view, or edit) based on their responsibilities within the study. To minimize potential contamination, we will implement several strategies: assign separate counselors to conduct MILAP and EUC sessions; restrict MILAP training to counselors delivering the intervention; and train both counselors and staff in controlled communication and contamination-mitigation techniques.Additionally, we have developed a research ethics brief to guide all study team members in the ethical conduct of the research involving vulnerable populations.(84)

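### MILAP women have up to nine more scheduled, unblinded safety check-ins in about the first three months, so any reading of the adverse event log by arm is exposed to unequal ascertainment

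*Protocol article*

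**What the plan says.** Under Safety monitoring & management, the protocol article states: "During each intervention and assessment session, counselors and assessment staff will check in with participants regarding any recent incidents of IPV". The same check-in covers other safety concerns, and the incidents are put on standardized forms. Under Adverse event reporting & harms {22}, the research coordinator keeps one adverse event log.

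The number of intervention sessions differs by arm. MILAP "includes nine sessions delivered over nine weeks to young women aged 15–24, their husbands, and MILs". For EUC, the description of the arm reads "These counselors will conduct an initial safety assessment and offer", followed by services, materials and referrals. EUC contacts beyond that first one do exist: the abstract says "EUC includes standard care, such as individual and group counseling for IPV", and the confidentiality section plans to "assign separate counselors to conduct MILAP and EUC sessions". No number or timetable is given for them.

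The assessments are the same in both arms: "We will conduct follow-up assessments at 1, 3 6, 9, and 12 months from baseline for all participants, regardless of intervention allocation". Sections {16b} and {17a} say that counselors learn the allocation and that assessment staff do not.

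Section {21b} gives the record its purpose: "we will document any adverse or serious adverse events to ensure participant safety and assess any potential risks associated with the MILAP". The sentence before it plans separate monitoring of IPV and depression severity.

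**The concern.** Incidents are actively sought wherever a session takes place, and one arm has many more fixed sessions. An event disclosed at a MILAP session may have no scheduled occasion to surface in EUC, and the person who hears it knows the arm.

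The Discussion names escalation of violence as a known risk of IPV interventions, so the safety record has to be readable. If the log is read by arm, equal true risk could look like harm from MILAP. Conversely, a real excess could be dismissed as the product of more contact. If the record does not show where an event was found, later analysis may be unable to separate these explanations. The trial status section dates the start of recruitment to April 2025, so events may already be accruing.

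**Working it through.** **Inputs**
- MILAP sessions (Table 1): hours 2+2+1+1+1+1+1+1+1 = 11 over 9 sessions, which reproduces the article's "Spanning nine weeks (11 total hours". The woman attends all nine: four with her MIL, four with her husband, one with both.
- Common follow-up assessments: 5 (months 1, 3, 6, 9, 12).
- Fixed EUC counselor contacts: 1. Further sessions: number not stated.

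**Step 1: scheduled contacts over 12 months**
- MILAP: 9 + 5 = 14.
- EUC: 5, or 1 + 5 = 6 with the initial safety assessment.
- Excess: 14 − 5 = 9, or 14 − 6 = 8. With m further EUC check-ins it is 8 − m.

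**Step 2: when the excess arises**
- Up to and including the three-month assessment: MILAP 9 + 2 = 11, EUC 1 + 2 = 3.
- After it: 3 v 3 (months 6, 9, 12).

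**Step 3: possible size, if every check-in is equally productive**

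Assume equal true risk, and let d be the chance that one check-in held after an incident detects it. With k such check-ins, P(detected) = 1 − (1 − d)^k. The documents do not give d.

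*Incident already present at the first contact (14 v 6).* At d = 0.10: 1 − 0.9^14 = 0.771 and 1 − 0.9^6 = 0.469, ratio 1.65. At d = 0.05, 0.20 and 0.40 the ratio is 1.93, 1.30 and 1.05.

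*Incident after the three-month assessment (3 v 3).* The ratio is 1.00 for any d.

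*Incidents spread evenly over 12 months.* I place the sessions at weeks 1 to 9 and the EUC initial assessment at week 1, and take a month as 4.345 weeks. Each term below is weeks × P(detected) at d = 0.10.
- EUC, first 13.035 weeks: 1 × 0.469 (k = 6) + 3.345 × 0.410 (k = 5) + 8.690 × 0.344 (k = 4) = 4.83.
- MILAP, first 13.035 weeks:
  - weeks 0–4 (k = 14, 13, 12, 11): 0.771 + 0.746 + 0.718 + 0.686 = 2.92
  - week 4–5: 0.345 × 0.651 (k = 10) + 0.655 × 0.613 (k = 9) = 0.63
  - weeks 5–9 (k = 8, 7, 6, 5): 0.570 + 0.522 + 0.469 + 0.410 = 1.97
  - the remaining 4.035 weeks (k = 4): 4.035 × 0.344 = 1.39
  - total, before rounding: 6.90
- Both arms thereafter: 13.035 × (0.271 + 0.190 + 0.100) = 7.31.
- Ratio for incidents arising in the first three months: 6.90 / 4.83 = 1.43.
- Ratio over 12 months: (6.90 + 7.31) / (4.83 + 7.31) = 14.21 / 12.14 = 1.17. The same calculation gives 1.24, 1.09 and 1.02 at d = 0.05, 0.20 and 0.40.

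**Step 4: a second model, by recall window**

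Suppose instead that a check-in captures everything in the preceding w weeks and nothing older. The share of the 12 months covered, on the same schedule with the EUC initial assessment counted, is:

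| w (weeks) | MILAP | EUC | ratio |
|---|---|---|---|
| 1 | 24.9% | 11.5% | 2.17 |
| 4 | 47.9% | 39.0% | 1.23 |
| 8 | 71.0% | 69.7% | 1.02 |
| 13.1 | 100% | 100% | 1.00 |

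If recall reaches back to the previous common visit, the imbalance disappears.

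**Step 5: direction**

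A family member attends every MILAP session, and the article does not say whether check-ins are private. In the extreme case of no disclosure at those sessions, an incident present at the start has 5 productive contacts in MILAP against 6 in EUC. At d = 0.10 this is 0.410 / 0.469 = 0.87, so the bias can also run the other way.

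**Step 6: after the fix**

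Counting only the common assessments gives 5 v 5 contacts, ratio 1.00 for any d that is equal in the two arms.

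**The case against.** The strongest reply is that the article plans no comparison of adverse event counts by arm. It describes case-by-case handling, with the DSMB judging relatedness. It also has a harm check with equal ascertainment: section {21b} monitors IPV and depression severity, and the IFVCS and PHQ-9 are given to both arms on one schedule by blinded staff. Event forms and tabulation rules usually sit in other documents.

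Much of this stands. No between-arm test of the log is stated, and the named risk is measured on a 63-item scale at visits common to both arms. The lack of a source field in an article is not itself a fault, and the form may already have one. What remains is that the article itself fixes where incidents are sought, and separately says that the documented events serve to assess MILAP's risks. Scale scores do not replace that record.

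A reader might infer more than the text supports:
- **Exactly nine extra check-ins.** This is an upper bound. The check-in wording is not limited to MILAP, and EUC sessions of unstated number exist.
- **Detection 65% to 93% higher over 12 months.** The ratios of 1.65 and 1.93 apply only to an incident present from the start. Contacts held before an incident cannot detect it.
- **A log biased against MILAP.** Step 5 shows that the direction is open.
- **Compromised primary outcomes.** They rest on the common assessments.

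**Conclusion.** The point holds in a limited form. As written, MILAP women have up to nine more scheduled check-ins than EUC women (eight net of the EUC initial safety assessment, fewer if EUC sessions include check-ins). These are made by unblinded counselors within about the first three months. A reading by arm of the adverse event record is exposed to unequal ascertainment in that period.

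Neither size nor direction can be fixed from the article. With equal true risk, equal disclosure at every contact and no EUC sessions beyond the initial assessment, the 12-month ratio runs from 1.02 to 1.24 for d between 0.40 and 0.05. Under the recall-window model it runs from 1.00 to 2.17. Lower disclosure in front of family could take it below 1, and more EUC check-ins would bring it towards 1. The values of d, the windows, the even spread of incidents and the week-by-week timing are assumptions. After the sessions end, scheduled contacts are equal. The IFVCS and PHQ-9 outcomes, and monitoring of them at the common assessments, are not affected. A change is worth making because it is cheap and the source of an event is hard to recover later.

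**What to change.** Record for each event how it was detected: assessment visit, intervention session or spontaneous report. Allow more than one source, so that an event found at a session still counts if it is also reported at an assessment. Without that, a rule crediting only the first source would remove events mainly from MILAP.

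State that the MILAP–EUC comparison of adverse events and IPV incidents uses those elicited by blinded staff at the common 1, 3, 6, 9 and 12-month assessments. Continue to give the DSMB all events, with session-detected and spontaneous events shown separately by source. State or record the number of EUC counselor contacts, so that the difference in exposure is known. Leave event management and reporting unchanged.

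The cost is one field on the event form, a count of EUC contacts and one sentence on the comparison. The downside is that the compared counts omit some session-detected events, although these remain listed.

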#### Adverse event reporting & harms {22}

The research coordinator will maintain an adverse event log and report incidents to research managers and the site PI. For serious adverse events, the research coordinator will immediately notify the site PI, who will inform the Ethical Review Board of the Nepal Health Research Council within 48 hours and submit a detailed report within two weeks. If multiple serious adverse events occur, the study team will review existing safety provisions and may temporarily pause the study. The site PI will also report serious adverse events to the Data and Safety Monitoring Board within three days and to the Institutional Review Board of the University of California San Francisco within 10 working days, in accordance with institutional guidelines. Adverse event determined to be unrelated to study participation will be securely stored at the study site office. The Data and Safety Monitoring Board will be responsible for determining whether an event is related to the study.

#### Frequency and plans for auditing trial conduct {23}

The site PI and research manager will conduct weekly reviews to monitor study implementation. The contact PI will perform monthly reviews to assess recruitment progress, participant retention, participant safety, and any methodological concerns. In accordance with reporting requirements, we will submit biannual recruitment and performance progress reports to the NIMH. Additionally, the study will undergo annual continuing ethical review by both the Nepal Health Research Council and the University of California San Francisco.

#### Plans for communicating important protocol amendments to relevant parties (e.g. trial participants, ethical committees) {25}

Any amendments to the trial protocol will be communicated to participants, members of the data safety and monitoring board, and relevant ethical/institutional review boards.

#### Dissemination plans {31a}

We will disseminate the findings of this study to multiple advisory boards, including the community advisory board and the data safety and monitoring board, as well as through various platforms such as peer-reviewed journals. We will share briefs, reports, and fact sheets to enhance accessibility. Additionally, we will present the study findings at regional, national, and international conferences to engage the broader research community. To support policy translation and impact, we will also conduct dissemination meetings with key stakeholders and policymakers following the completion of trial.

## Discussion

This study introduces MILAP, an innovative family-based intervention designed to address two deeply interconnected public health challenges, IPV and depression, which disproportionately burden young women in Nepal and other LMICs. In these settings, women often live in multi-generational households with limited autonomy and few options to leave abusive relationships. By leveraging family dynamics, MILAP offers a culturally grounded, non-stigmatizing approach that fosters resilience and empowerment at multiple levels. At the intrapersonal level, it equips women with essential coping and emotional regulation skills. At the interpersonal level, it strengthens bonds between MILs and DILs, and enhances spousal communication and trust. At the family level, it cultivates a supportive household environment that promotes women’s freedom of movement and overall well-being.

This randomized controlled trial will generate robust evidence on the effectiveness of family-based intervention like MILAP, that engages a woman, her husband and her MIL, to simultaneously reduce IPV and depression. In addition, we will conduct a cost-effectiveness analysis to estimate the health and economic benefits of scaling up MILAP in Nepal. The findings will inform decisions on broader implementation by demonstrating MILAP’s value relative to enhanced usual care in reducing IPV and improving mental health outcomes.

This study has multiple strengths. The intervention design, recruitment plans, retention strategies, and safety protocols are all informed by our pilot studies, input from the community advisory board and prior behavioral health research in the region. Rather than directly focusing on the stigmatized issues of IPV and depression, MILAP frames the intervention as a pathway to building healthier relationships, which was found to be acceptable and engaging in our pilot study. We have developed a robust recruitment and retention plan that leverages trusted community-based organizations, community advisory boards and mobilized community health workers to ensure sustained engagement. A known risk in IPV interventions is the potential escalation of violence. While pilot findings suggest MILAP does not increase IPV risk, we have developed rigorous safety protocol and will have a data safety and monitoring board set up to regularly review safety data.

The study may face some limitations. First, we will exclude severe IPV cases requiring hospitalization because such severe cases are unlikely to benefit from a behavioral intervention like MILAP. Although these cases represent a small minority, this exclusion limits the overall reach of the intervention. Second, although our pilot data showed high completion rates and the community advisory board confirmed that nine sessions are reasonable, there remains a risk that the completing all nine sessions may be burdensome for some participants. To reduce assessment-related burden, participants will receive modest compensation for their time and travel, and MILAP counselors will be provided with protected time to deliver MILAP.

IPV and mental health challenges require culturally responsive solutions that empower women while engaging key family influencers. MILAP has the potential to how IPV and depression are addressed, not only in Nepal but also in other socio-culturally similar contexts. If successful, this study will establish MILAP’s effectiveness, cost-effectiveness, and mechanism of change, shedding light on critical pathways such as FOM and women’s autonomy that drive positive transformations in IPV and mental health outcomes.

